### Aims and Objectives

This study aims to test (1) the potential of pop-up messages as a prevention measure in a gambling setting and (2) whether this potential is moderated by characteristics of people exposed to the messages. Secondary aims also tackle some fundamental assumptions of gambling studies conducted in a laboratory setting.

Specifically, the main objectives are to test to what extent prevention pop-up messages affect participants:

Gambling behaviors (eg, money betted, gambling session length, gambling intensity, etc).Cognitions (eg, thoughts elicited by messages, perceived effectiveness of message, etc).Emotions (eg, enjoyment of gambling, emotional response to messages, etc).

Secondary objectives are:

To test to what extent the main effects are moderated by participants’ characteristics (eg, gender, age, education, Problem Gambling Severity Index [PGSI] category, etc) moderate the main effects found in objectives 1‐3.To examine the feasibility of studies conducted in a laboratory setting with the use of real money (or using deception to make the participants believe they are gambling their own money). This objective is accomplished with the use of five research questions:5.1. Is it possible to recruit enough participants for the study to conduct meaningful statistical analysis (ie, does the novel approach of risking one’s own money in a study without guaranteed compensation deter too many people from participating)?5.2. Does the laboratory bar replicate adequately the overall “vibe” of a typical gambling venue with EGMs?5.3. Do the participants find their actual gambling activity in the bar replica as realistic as a real one?5.4. Do the participants believe they are gambling their own money during the study (ie, to what extent does the deception work)?5.5. Do outcomes, both self-reported (past 12 months) and measured in the laboratory, differ from each other?

## Methods

### Ethical Considerations

This study was approved by the Comités d'éthique de la recherche avec des êtres humains de l'Université Laval (CÉRUL; reference 2020-076 A-1 / 27-05-2024). Preliminary consent is obtained verbally during the intake interview and confirmed with a signature just before the gambling session in the laboratory. Some aspects of the study are withheld from the participants and are only revealed during debriefing after the gambling session has ended (see "Duplicity" and "Gambling session in the laboratory" subsections of the "Methods" section for details). After debriefing, participants are asked to confirm their consent one last time. Participants can remove consent at any point of the study without prejudice. After debriefing, participants who wish to quit without completing the study can ask that all their data be destroyed. Compensation for participation can vary between CA $30 and CA $500 depending on the results of the gambling session, which is completely random (see "Presentation of the Study and Verbal Consent" and "Duplicity" subsections of the "Methods" section for details). Some transportation expenses were also reimbursed on top of the compensation, namely transit fare, parking validation at the university, and taxi for the elderlies and people with mobility impairments. All data is kept in secured servers (files) and locked drawers (physical forms). Participants' data is anonymized with a nonsequential ID number.

This study exposes participants to potentially stressful situations. Notably, by gambling with their own money, participants risk gambling more than what they can afford and find themselves in a situation where they think they have lost a lot of money. This stress is a byproduct of the duplicity required to ensure maximal ecological validity of the study. It is mitigated by the fact that any potential stress is limited to a maximum of 2 h (the time limit for the study), after which debriefing ensues and they learn their “lost money” will be returned to them.

The use of duplicity poses some concerns over the importance of free and informed consent. While participants initially enroll in the study without knowing all the parameters, they have the option to retroactively remove their consent and ask for the destruction of their data during the debriefing. Some steps are also taken to minimize aspects of the study that are masked by duplicity. For example, even though losses are reimbursed to participants, gains are still paid as advertised. This prevents a potential situation where a participant who wins a lot of money and expects to leave with it is instead given a standardized (and lesser) amount.

It is also worth noting that this study does not expose participants to higher levels of risk and stress than what they already frequently experience in their own lives. Inclusion criteria target participants who regularly gamble on EGMs in their everyday lives. In the context of the study, participants are provided with the same incentives to gamble, but nothing is done to exacerbate these behaviors (eg, altering the EGMs’ payout rate, offering loans to gamble, etc). On the contrary, half the participants are provided with prevention messages, and any money lost while gambling is reimbursed at the end of the session. Also, because this study is conducted in a psychology laboratory, people on site can provide crisis support should a participant feel unwell after a significant loss. This kind of support is not usually available where EGMs are situated. Finally, we chose not to recruit the most vulnerable gamblers (ie, people trying to reach or maintain abstinence). Despite those protections, the ethics committee felt that probable pathological gamblers should also be excluded from the study.

### Study Design

This is a 2-arm stratified block randomized controlled study. Participants are randomized to one of the two arms in a 1:1 ratio:

Experimental group: Regular gambling session with prevention pop-up messages presented on a fixed schedule.Active control group: Regular gambling session.

There are 3 assessment phases in this study (see Figure 1). Recruitment began in February 2024 and concluded in December 2024. Study completion is expected in February 2026. Study outcomes will be reported in line with the Consolidated Standards of Reporting Trials guidelines and the extension for social and psychological interventions trials (CONSORT-SPI) [75].

**Figure 1. F1:**
[figure not shown]
Schematic overview of the 2-arm stratified block randomized controlled trial. EGM: electronic gambling machine; PGSI: Problem Gambling Severity Index.

### Sample Size Considerations

Using G*Power, we estimated the required sample size for an α level of 5% and ß level of 80% for a 2-tailed *t* test for a range of effect sizes (see Table 1). This was done both for testing differences in outcomes between 2 independent groups and for repeated measures.

**Table 1. T1:** Required sample size for a range of effect sizes.

Effect size (*g*)^a^	Per group, n (%)	Total, N
0.2	394 (50)	788
0.3	176 (50)	352
0.4	100 (50)	200
0.5	64 (50)	128
0.6	45 (50)	90
0.7	34 (50)	68
0.8	26 (50)	52
0.9	16 (50)	32

a Calculated for an α level of 5% and ß level of 80% for a 2-tailed *t* test.

A recent meta-analysis by Bjørseth et al [18] on the effects of RG pop-up messages on gambling behaviors and cognitions reports effect sizes respectively of *g*=0.62 (95% CI 0.36-0.87 and *g* 0.58 (95% CI 0.33‐0.83) when adjusting for publication bias. Based on those values, the total sample size would be between 86 and 96. Note that sample size requirements for 1-way analysis of covariances (ANCOVAs) and repeated measures analyses would be equal to or smaller. Considering the potential difficulty in recruiting participants accepting to play with their own money, we aimed at a sample size of 80. Therefore, we can expect a power range from 72.34% to 77.66% with effect sizes comparable to what is reported by Bjørseth et al [18].

### Participants and Eligibility Criteria

We aim to recruit 80 participants in total. While many may refuse to participate when presented with the study’s specifics, we do not anticipate a significant number of dropouts after consent is obtained. Textbox 1 shows the inclusion and exclusion criteria.

Textbox 1.Eligibility criteria.Inclusion criteria:Aged 18 years and older.Functional literacy in French.Having played electronic gambling machines (EGMs) at least once every 2 weeks for the past 12 months. Note that this criterion was subsequently lowered to having played EGMs at least 6 times in the past 12 months to expand the recruiting pool. This change was done on May 27, 2024.Exclusion criteria:Classified as a probable pathological gambler (score ≥8 on the Problem Gambling Severity Index, PGSI).Currently receiving treatment for problem gambling or trying to achieve or maintain abstinence from gambling.Currently under self-exclusion from a gambling venue or website.

The rationale for the age cut-off is that it is the legal age to gamble where the study is conducted (Quebec, Canada). The literacy requirement is justified by the fact that this study is conducted in French and requires being able to read and understand simple texts in that language. Questions are also asked and answered in French.

The age cut-off is the legal age to gamble where the study is conducted (Quebec, Canada).

The rationale for a floor limit on play frequency is that prevention pop-up messages are expected to produce a small effect that becomes more impactful when cumulated over multiple sessions. Therefore, these messages are thought to be more suited to people who gamble on a regular basis. Furthermore, regular EGM gamblers are more likely to feel compelled by a message warning about the dangers of excessive gambling than people who gamble very sporadically.

The rationale for a floor limit on play frequency is that prevention pop-up messages are expected to produce a small effect that becomes more impactful when cumulated over multiple sessions. Therefore, these messages are thought to be more suited to people who gamble on a regular basis. Furthermore, regular EGM gamblers are more likely to feel compelled by a message warning about the dangers of excessive gambling than people who gamble very sporadically.

The rationale for the exclusion criteria is ethical considerations. The first criterion is mandated by the ethics committee to prevent possible adverse effects on the most vulnerable gamblers. The other 2 criteria aim not to interfere with someone’s recovery process or wishes to stop gambling.

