### Statistical Methods

Sociodemographic variables, past 12 months of gambling-related variables, and PGSI category will be presented in a table with appropriate central tendency estimates. This table will be divided by assignation group.

A total of 3 statistical models will be used to analyze the outcomes presented in Tables3  4. All these models will control for the time-varying covariate “gains-losses differential” (ie, remaining balance on the EGM at measured time point minus money inserted in the EGM from the start of the study). All models will also test the moderation effect of the following variables: gender (men or women), age (continuous), education (5 categories), and PGSI category (nonproblem, low risk, and moderate risk). Holm-Bonferroni correction [85] will be used to counteract family-wise error rate due to multiple comparisons in each model for each statistically significant categorical variable (ie, time for repeated measures ANCOVAs; moderators with ≥3 categories).

The first model uses ANCOVAs to examine the differences between the two groups at the end of the gambling session on outcome variables 1, 3, 4, 6‐9, 14, 16, 17, and 19, separately.

The second model uses repeated measures ANCOVAs to examine the differences between the two groups at specific time points during the experiment corresponding to the presentation of the prevention pop-up messages in the experimental group. This model is computed on outcome variables 1 and 10‐13, separately.

The third model uses repeated measures ANCOVAs to examine the differences between self-reported measures (past 12 months) and the observed behaviors during the experiment. This model is computed on outcome variables 2, 5, 15, and 18, separately.

Secondary and other outcomes will be documented but will not be statistically compared. Descriptive estimates will be provided for each quantitative variable. Open-ended questions will be analyzed in a manner inspired by the thematic analysis method (see Textbox 3) [86].

Textbox 3.The 5 steps in analysis of open-ended questions.Interviewer’s notes are regrouped in a Microsoft Word document.Raw data is carefully read, both by main author and another member of the research team, to extract categories of similar content.Categories are refined by both coders.Raw data is independently categorized in appropriate categories by both coders.Intercoder agreement is calculated on all categorizations to ensure reliability.

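### The play-frequency floor fell from about 26 to 6 plays a year during recruitment, but the analysis neither adjusts for baseline play frequency nor reports the effect by it, and the limitations do not mention the change

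*Protocol article*

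**What the plan says.** All places are in the protocol article.

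- **Participants and Eligibility Criteria, Textbox 1.** The inclusion criterion was electronic gambling machine (EGM) play "at least once every 2 weeks for the past 12 months". Later, "this criterion was subsequently lowered to having played EGMs at least 6 times in the past 12 months", with the purpose and date given as "to expand the recruiting pool. This change was done on May 27, 2024".
- **Same section, rationale for the floor.** It remains in place after the change: "these messages are thought to be more suited to people who gamble on a regular basis", and "regular EGM gamblers are more likely to feel compelled by a message warning about the dangers of excessive gambling than people who gamble very sporadically".
- **Ethical Considerations.** The sample is still described as regular players: "Inclusion criteria target participants who regularly gamble on EGMs in their everyday lives".
- **Study Design.** "Recruitment began in February 2024 and concluded in December 2024".
- **Randomization.** Strata are PGSI categories only.
- **Statistical Methods.** Every model controls for one covariate, the gains-losses differential. For moderation: "All models will also test the moderation effect of the following variables: gender (men or women), age (continuous), education (5 categories"), followed by PGSI category. Play frequency is in neither list. Past-12-month gambling variables are tabulated by group.
- **Strengths and Limitations.** Recruitment difficulty and the exclusion of probable pathological gamblers are discussed. The lowered floor is not.

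**The concern.** The protocol gives a reason to expect the response to the messages to vary with how often a person plays. It then admitted people who play much less often, and the analysis did not follow. This is not detail left to an unseen analysis plan: the article itself names the covariate and the moderators for all models.

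Two things are at stake. The first is interpretation. The estimated effect is an average over a wider range of players than the rationale and the ethics section describe, and the planned analyses would not show how it varies over that range. The second is precision. If yearly play frequency predicts money or time in the session, leaving it out gives up some power in a trial that already accepts less than 80%.

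**Working it through.** **1. Size of the change.** Once every 2 weeks is 365/14 = 26.1 plays a year. The new floor is 6. The reduction is 1 − 6/26.1 = 77%. The change on May 27 leaves about 7 of the 11 recruitment months (February to December 2024) under the lower floor. Months are not participants, and fortnightly players could also enter after the change, so this does not give the share who entered below the old floor.

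**2. The plan's own power.** Inputs from Sample Size Considerations: N=80, two-sided α 0.05, g=0.58 and 0.62. With 1:1 allocation there are 40 per arm. Two-sample t test, noncentrality g·√(40·40/80) = g·√20, 78 degrees of freedom:

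| g | Power | Plan states |
|---|---|---|
| 0.58 | 72.6% | 72.34% |
| 0.62 | 78.2% | 77.66% |

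The plan's figures reproduce to within a percentage point.

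**3. Illustration of dilution.** Everything that drives this step is assumed: g=0.60 in those meeting the fortnightly floor, g=0.30 in the others, and a share s of others. Average g = 0.60(1−s) + 0.30s.

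| s | Average g | Power, 40 per arm |
|---|---|---|
| 0% | 0.60 | 75% |
| 30% | 0.51 | 62% |
| 50% | 0.45 | 51% |
| 60% | 0.42 | 46% |

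Under the harsher assumption of no effect at all in the others, and g=0.58 to 0.62 in the rest, power is 54–59% at s=20% and 25–28% at s=50%.

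**4. What an interaction test could show.** For a two-level split, SE of the difference in g ≈ √(4/(80s) + 4/(80(1−s))). At s=50% this is √(0.1+0.1) = 0.447. For a difference of 0.30 the ratio is 0.30/0.447 = 0.67, giving power of 10%. At s=30% power is 9%, and at s=60% it is 10%. For a difference of 0.60, power is 23–27% over the same shares.

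**5. What the original-criterion subset could show.** With s=30%, 50% or 60%, 56, 40 or 32 people remain. Power for g=0.60 is 60%, 46% or 38%.

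**6. What the covariate could gain.** Adjusting for a baseline variable with correlation r to the outcome raises the effective g to g/√(1−r²). The correlation is assumed; the documents give none. At g=0.60, r=0.3 gives 0.629 and 79% power; r=0.5 gives 0.693 and 86%. At r=0.1 power is 76%, so the gain is negligible if frequency predicts little.

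**The case against.** - **The change does not contradict the rationale.** A reader might infer that it does. The rationale argues for a floor without naming a number, six a year is still a floor, and very sporadic play is not defined. One leg of the rationale concerns benefit built up over many sessions, which a single-session trial does not measure. Only the sentence on feeling compelled bears on the measured effect. This stands: it is a tension.
- **Frequency is not the only characteristic tied to response.** The section on designing messages names stage of change, and the limitations name luck in gains and losses, which is the covariate used. The limitations also suggest a smaller effect in pathological gamblers and say that regular play overlaps with that group, so even the direction of any frequency gradient is uncertain. This stands.
- **The dilution figures are assumed.** The share, the halving, and the reading of the meta-analytic g as the effect in fortnightly players are all outside the documents. Six plays is a minimum and not a typical value. This stands.
- **Randomization protects the comparison, and the change is dated and disclosed.** Both are true. Neither gives a reader the effect by play frequency.
- **PGSI category may serve as a proxy.** PGSI is stratum and moderator, but it measures problem severity, and the document does not offer it as a stand-in for frequency.
- **The moderator list is open.** Objective 4 ends its examples with an etcetera, but the Statistical Methods section fixes the list.
- **Frequency may not be on file as a count.** Screening had to ask about it to apply the criterion, and intake covers past-12-month EGM behaviors. The form in which it was stored is not stated.

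**Conclusion.** The floor was lowered by about 77% while the stated rationale and the description of the sample stayed the same, and neither the covariate list, the moderator list nor the limitations took account of it. This affects precision and interpretation. It does not bias the randomized comparison.

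A reader might go further and infer that the average effect conceals a null in occasional players, or that power has fallen to about 50%. The documents do not support either, because they give neither the share below the old floor nor the effect in that group. The power figures show only how sensitive the trial would be if the assumed values held. Nor would a frequency interaction separate a true null from dilution: at about 10% power for 0.60 versus 0.30, it cannot. The part of the remedy that does not depend on that test is the covariate, and its gain depends on how well frequency predicts the outcomes, which is unknown here.

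**What to change.** Recruitment is over, but the article reports no results, so the following can still be fixed before analysis.

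1. Add baseline past-12-month EGM play frequency, continuous and suitably transformed, as a covariate in the between-group models. Keep the four listed moderators.
2. Report frequency-by-arm moderation, and the effect in participants who meet the original fortnightly floor, as exploratory estimates with confidence intervals. Define that subset by reported frequency and not by entry date.
3. State the lowered floor as a limitation, and bring the description of the sample in the ethics section and the rationale into line with the criterion in force. Report how many participants entered below the original floor.

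Cost: wording, about one degree of freedom for the covariate, and one exploratory subset estimate. The exploratory parts have low power, and the report should say that a non-significant interaction does not rule out a weaker effect in occasional players. If frequency was recorded only as meeting or not meeting a floor, that indicator is the fallback.

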### Recruitment

From February 2024 and on, the study was advertised online via social media, our research team’s website, and our university’s mailing list. An email was also sent to participants from a previous study who agreed to be contacted again. The study was advertised offline via ads in a local newspaper 2 times in February 2024. Recruitment posters were placed in gambling venues in the same city of our university.

To boost recruitment, we started a second recruitment wave during the summer of 2024. This wave mainly used online ads targeted at people geolocated at gambling venues. Inclusion criteria were also relaxed on minimal gambling frequency (see the “Participants and Eligibility Criteria” section).

### Preexperimentation Phase

#### Screening

Screening and following interview for the preexperimentation phase are done over the phone. Participants are asked questions to determine if they satisfy the inclusion and exclusion criteria. Not all criteria are communicated on the recruitment ads, and neither are the participants told beforehand what answer would disqualify them. The screening interview ends with the PGSI, which is a subscale of the Canadian Problem Gambling Index [6]. This instrument is designed to determine problem gambling severity and is the actual gold standard for problem gambling screening in the general population. The instrument is composed of nine items scored on a 5-point Likert scale. Scores range from 0‐27 and classify gamblers in four categories: (1) nonproblem (score of 0), (2) low risk (score of 1‐2), (3) moderate risk (score of 3‐7), and (4) problem gambling (score ≥8).

#### Presentation of the Study and Verbal Consent

After satisfying the screening criteria, participants are presented with the details of the study. Participants are recruited for a single gambling session in a bar replica equipped with EGMs. Recruitment is done under the false pretense of evaluating the realism of a gambling session in a laboratory replicating a bar. The main points communicated to the participants during the presentation of the study are:

Gambling is done with your own money. You must bring the amount they wish to gamble the day of the experiment.Winnings are paid up to CA $500 more than the total amount inserted in the EGM over the course of the gambling session (eg, if you insert CA $60 in the EGM during your session, you could be paid up to CA $560). In turn, losses are real. There is no baseline compensation for participating in the study. The only compensation for participation is the potential winnings made while gambling. Overall, it is possible to end the study with less money than at the beginning, even to lose it all.The EGMs used in this study are of the same model currently in operation in Quebec, Canada. Their payout rate is the same (92%).You are free to gamble as much and for as long as you like.You are allowed to take breaks.Snacks and nonalcoholic beverages can be purchased with real money during the study via cash or electronic transactions.

Participants who give their verbal consent proceed with the intake interview.

